#### Embedded health economic study

Data generated from our feasibility study [5, 13–19] provided important insights to optimise the design of the economic evaluation in this definitive RCT. This includes selection of the most appropriate Health-related quality of life (HRQoL) instrument, as well as defining the most appropriate methods and data collection tools. The economic analysis of this study will be based on an assessment of the incremental cost per successfully treated child (primary outcome) and the incremental cost per Quality Adjusted Life Year (QALY) gained.

In our feasibility study, following a detailed micro-costing approach, we established the potential of economic savings for the NHS [5, 15]. Alongside this RCT, we will conduct a full economic evaluation assessing the cost-effectiveness of the non-operative treatment pathway compared to appendicectomy. Therefore, the within trial economic analysis, adherent to guidelines for good economic evaluation practice [22–24], will include (i) a cost-effectiveness analysis (CEA) using the primary outcome at the end of the follow-up (1 year) and (ii) a cost-utility analysis (CUA) using HRQoL (caregiver-reported CHU-9D) collected at the 6-week visit to assess the short-term impact of the intervention in terms of QALYs.

The perspective of the economic study will be that of the NHS. All cost-effectiveness results will be presented on (i) the cost-effectiveness plane, which captures the uncertainty around the results showing the incremental costs and incremental effects of the comparison of interest in a 2-dimentional plot, and (ii) the cost-effectiveness acceptability curves, which graphically represent the uncertainty in terms of probabilities, regarding the cost-effectiveness of the intervention. We will also report on the economic implications for the NHS of non-operative treatment pathway. This will include developing and reporting a tariff for the non-operative treatment of uncomplicated acute appendicitis since this is not currently available within the NHS Reference Costs data.

### Data collection and health economic outcomes

#### Resource use, costs and HRQoL data

In accordance with findings of our feasibility study [5, 13–19], the primary care data from parents will be collected by research nurses during phone calls and in person interviews using a short modified version of the CSRI (Client Service Resource Inventory) questionnaire [25–27]. For secondary care data, we will use the Patient Level Information and Costing Systems (PLICS) [28] data for acute services records activity and cost information for admitted patient care, outpatient appointments and A&E attendances. The results from our feasibility study support the use of PLICS data as a reliable alternative to micro-costing [5]. Unit cost will use the NHS Reference Costs [29] and Personal Social Services Research Unit (PSSRU) [30] data in addition to other unit costs as appropriate. To allow reporting in QALY terms, we will use the caregiver-reported CHU-9D.

#### Timing of health economic data collection

The data collection refers to hospital records for admission(s) to hospital(s) up to 12-month duration, including admissions for recurrent appendicitis and/or other related admissions. Data regarding health care resource use will be collected directly from parents/guardians through a smartphone app weekly up to 4 weeks following randomisation. These records will be discussed in detail during a face-to-face visit at 6 weeks. Health economics (HE) data will be collected during phone calls at 4-, 8- and 12-month visits, and the e-CSRI questionnaire will be completed by a research nurse during these visits at 6 weeks and 4, 8 and 12 months.

Our previous work revealed that timing is an important consideration for collecting QoL data and estimating QALYs for this intervention. While there was a significant difference in QoL at 2 weeks, this difference was not present at 6 weeks, by which time both groups had returned to almost full health. Therefore, we will record QoL data at baseline, weekly up to 4 weeks and then at 6 weeks, in order to identify the return to full health and normal life for children in both arms. The CUA will report these short-term outcomes in QALYs.

### Participant timeline {13}

Table 4 shows the participant timeline for patient’s observations and procedures.

**Table 4 Tab4:** Schedule of observations and procedures

**Visit/time point (all measured from randomisation:**	**Baseline/randomisation**	**Treatment**	**Dis-charge**	**1 week**^**a**^ (+ 3 days)	**2 weeks**^**a**^ (+ 3 days)	**3 weeks**^**a**^ (+ 3 days)	**4 weeks**^**a**^ (+ 3 days)	**6 weeks** (− 1 week/+ 2 weeks)	**4 months**^**a**^ (− 1 week/+ 2 weeks)	**8 months**^**a**^ (− 1 week/+ 2 weeks)	**12 months**^**a**^ (− 1 week/+ 2 weeks)
Informed consent	**X**										
Eligibility evaluation	**X**										
Medical history	**X**										
Diagnostic tests as per standard practice (blood test—Total WBC/CRP/Neutrophil, CT scan, Ultrasound)	**X**										
Pregnancy test^b^	**X**										
Physical exam (abdomen exam)								**X**			
Vital signs (temperature)	**X**										
Randomisation	**X**										
Appendicectomy (arm B only)		**X**									
IV antibiotics (arm A only)		**X**									
Doctor/healthcare professional assessment	**X**							**X**			
Histology following surgery								**X**	**X**	**X**	**X**
Discharge assessment			**X**								
Adverse Events	**X**		**X**	**X**	**X**	**X**	**X**	**X**	**X**	**X**	**X**
Health economics—resource use	**X**		**X**	**X**	**X**	**X**	**X**	**X**	**X**	**X**	**X**
CHU-9D	**X**			**X**	**X**	**X**	**X**	**X**	**X**	**X**	**X**
Patient data collected on app				**X**	**X**	**X**	**X**				
Client service receipt inventory (CSRI)								**X**	**X**	**X**	**X**
Recurrence								**X**	**X**	**X**	**X**
Complication requiring intervention under general anaesthesia	**x**							**x**	**x**	**x**	**x**

^a^To be collected remotely via phone call and/or app

Data collected on app:

▪ Pain relief taken Y/N

▪ CHU 9D proxy and self-report where appropriate

▪ Antibiotics taken Y/N

▪ Able to do normal daily activities Y/N

▪ Attended school Y/N

▪ Able to do full activities Y/N

▪ Parents missed work Y/N

▪ The last week have you had any contact with a health care professional(s) for your child’s appendicitis? Y/N

^b^Only for those of childbearing potential

NB: The Participant/legal representative is free to withdraw consent at any time without providing a reason. When withdrawn, the participant will continue to receive standard clinical care. Follow up data will continue to be collected (unless the participant/legal representative has specifically stated that they do not want this to happen)

### Sample size {14}

We will test the hypothesis that non-operative treatment pathway is non-inferior to appendicectomy. We anticipate a difference between the treatment arms with respect to the primary outcome of 8 percentage points (assuming 88% treatment success in the appendicectomy group and 80% in the non-operative group). Since there are potential further benefits to non-operative treatment that are not included within the primary outcome (e.g. greater parental acceptability, avoidance of general anaesthesia, avoidance of surgical complications, cost), it is appropriate to use a wider non-inferiority margin for our analysis. The size of this non-inferiority margin was explored with both surgeons and parents in our feasibility study [5, 13–19], which was pre-specified at 20% for this trial. Of interest, this is the same margin that was defined by a Cochrane review as being ‘clinically relevant’ [31].

Given that the assumed difference in success rate is non-zero (8%), a one-sided 5% significance level was deemed appropriate. Based on the estimates of non-zero assumed difference of 8% and non-inferiority margin of 20%, with a one-sided 5% significance level and 90% power, this trial will require a total of 318 cases analysed at 1 year (159 per arm). Allowing for 15% loss to follow up, the recruitment target will be 376 participants (188 per arm).

### Recruitment {15}

Recruitment will be performed by surgeons and supported by research nurses since parents do not feel it is appropriate to be recruited into this trial by anyone other than a surgeon, as it was found in our preparatory work with the National Institute of Health Research Clinical Research Network (NIHR CRN) (Children) Young Person’s Advisory Groups (YPAGs). The CRN has also indicated that they do not think it is appropriate for nurses to recruit to this study alone due to the nature of the intervention which will challenge commonly-held beliefs about appendicectomy as best treatment for appendicitis, and the relatively short timeframe necessary for a decision to be made. Therefore, we will utilise members of the clinical team (Specialist Surgical Trainees and Consultants) to recruit patients to the study in conjunction with research nurses. Recruitment capacity will therefore be available 24 h per day.

Parents will be approached by a member of the surgical team (with or without a research nurse) who will explain the study to them and invite them to participate. Prior to this discussion, verbal permission will be taken for the recruitment discussion to be voice-recorded. The CONTRACT 2 trial will be explained to parents and children with the aid of age-specific information sheets and a short video presentation. The patient video will also be made available via a web-link to allow parents/guardians, who cannot be in hospital with their children at the time of recruitment, to access the same trial information as the consenting parent/guardian.

We will provide an educational package to clinical staff at each centre. This will include (i) educational evenings at or near each centre (or delivered remotely via videoconference) to which all members of the clinical team will be invited (core and specialist surgical trainees, research nurses and consultant surgeons); (ii) a short video to be shown to potential participants during the recruitment process; and (iii) age-appropriate participant information sheet and consent form.

#### Embedded communication sub-study

A qualitative sub-study is embedded during the pilot phase of this RCT with an aim to identify potential barriers to recruitment and enhance informed consent. This communication sub-study was designed learning from our experience in our feasibility study [5, 13–19]. We will develop and deliver bespoke communication training to optimise surgeons’ communication about the trial, and families’ experiences of being approached. We will identify potential recruitment issues by monitoring recruitment at all sites and request sites to audio-record consultations. Researchers will review consultation recordings to inform bespoke trial communication training, which we will provide to all sites on an ongoing basis during the internal pilot.

#### Method

The communication sub-study team will provide sites with encrypted audio-recording devices. During the internal pilot, surgeons and research nurses (recruiters) will routinely seek verbal permission to audio-record consultations with families during which: CONTRACT 2 is discussed before consent is sought, consent is obtained and the family is informed of their treatment allocations. Recruiters will briefly outline the purpose of audio-recording the consultation and record the consultations if permission is granted. At the end of the consultation or at the point of taking consent for the trial, recruiters will obtain written consent for the audio-recording to be used in the sub-study. If the family declines to provide written consent, the audio-recording will be deleted. If the family provides written consent the audio recording will be transferred to the researchers via a secure encrypted system. A member of staff will also obtain written consent and complete a proforma that will capture fields providing details of the consultation, such as the name of recruiter, date of the consultation, patient age, RCT participation status and treatment allocation. Audio recording will be transcribed. The communication sub-study research team will listen to and review samples of recruitment consultations to inform bespoke feedback for each site.

#### Plan for bespoke training

Before trial recruitment starts, the communication sub-study team will deliver an initial trial communication group training session to optimise surgeon and research nurse communication with families about the trial. All recruiters who will be involved in recruiting to the trial will be invited to attend the event. This session will be based on the successful QUINTET programme [32] and will also incorporate key findings from the CONTRACT Communication Study based on our feasibility study [5, 13–19]. Training will cover key themes, such as avoiding misinterpreted or misunderstood terms, exploring family treatment preferences and highlighting families’ frequently asked questions.

We will also develop and disseminate a package of resources and support materials informed by recruiter feedback in our previous work [16] and in consultation with site staff. This includes a demonstration video that incorporates key learning points from our feasibility study [5, 13–19] and a ‘hints and tips’ handout. The ‘hints and tips’ handout will be regularly updated and circulated during the internal pilot stage, in response to ongoing review of the RCT consultations.

During the pilot stage, we will identify and offer additional support refresher training to sites that might benefit from it (e.g. those with lower approach/recruitment rates or those that have encountered challenges in discussing the trial in a balanced way with families). This will involve reviewing recruitment consultations and visiting such sites to support the team (or deliver training via video call if more appropriate) during months 3–9 of the pilot stage.

## Assignment of interventions: allocation

### Sequence generation {16a}

Patients enrolled in the trial are randomised to groups (1:1 ratio) online allowing instant assignment to treatment group 24 h per day.

Minimisation is used to ensure similarity between the groups in factors that may affect diagnostic accuracy and outcome of treatment using the following criteria:(i)Age: 4–8 years; 9–15 years(ii)Sex: Male; Female(iii)Duration of symptoms (onset of pain to recruitment into study): < 48 h; ≥ 48 h(iv)Centre

### Concealment mechanism {16b}

The online randomisation system allows complete pre-randomisation concealment of treatment allocation.

### Implementation {16c}

Once informed consent is received and eligibility for the trial is confirmed, the patient is enrolled in the trial and randomised to a treatment group (1:1 ratio) via an independent, web-based system (TENALEA) operating 24/7. The treatment group allocation will be instantly revealed to both the patient/parent and the clinical team.

## Assignment of interventions: blinding

### Who will be blinded {17a}

Due to the nature of the interventions in this trial, there will be no blinding of participants or investigators.

### Procedure for unblinding if needed {17b}

The trial design is open-label, therefore there is no unblinding procedure.

## Data collection and management

### Plans for assessment and collection of outcomes {18a}

Data will be collected at baseline by clinical teams, during hospital stay by research nurses and during follow-up period directly from parents via smartphone App or paper card at weeks 1–4 and by research nurses in other time-points. All data will be collected prospectively to ensure high accuracy and entered into an online secure trial database (Medidata) as soon as is practically possible after collection. Sites will be trained in all aspects of trial delivery including data collection in site initiation visits.

### Plans to promote participant retention and complete follow-up {18b}

Patients completing all follow up appointments and questionnaires will be offered a gift voucher (via email) as a thank you for taking part in the trial. Participants are informed of this in the trial information sheet when considering their participation in the trial.

Where possible, patients who have withdrawn from their allocated treatment will remain in follow-up as per the trial schedule. If patients additionally withdraw consent for this, they will revert to standard clinical care as deemed by the clinician responsible. It would remain useful for the trial team to continue to collect standard follow-up data and, unless the patient explicitly states otherwise, follow-up data will continue to be collected.

### Data management {19}

Participant data will be entered remotely at site and retained in accordance with the current Data Protection Regulations. The PI is responsible for ensuring the accuracy, completeness and timeliness of the data entered.

The participant data is pseudo-anonymised by assigning each participant a participant identifier code which is used to identify the participant during the trial and for any participant-specific clarification between the clinical trial unit and site. The site retains a participant identification code list which is only available to site staff.

### Confidentiality {27}

The confidentiality of participants taking part in the trial will be preserved. Investigators will ensure that participant’s anonymity is maintained. Identification codes rather than names will be used for all trial activities for all participants.

Any data collected as part of the trial will be securely stored in line with the Data Protection Act and General Data Protection Regulation.

### Plans for collection, laboratory evaluation and storage of biological specimens for genetic or molecular analysis in this trial/future use {33}

Not applicable for this trial, no samples collected.

## Statistical methods

### Statistical methods for primary and secondary outcomes {20a}

The analysis of the primary outcome (treatment success at 1 year) will be based on an intention-to-treat (ITT) population, which includes all children who have been randomised to a treatment arm (non-operative treatment pathway or appendicectomy), regardless of compliance or treatment received, and have completed data for the outcome and timepoint being analysed. Primary analysis will be by a mixed effects logistic regression model controlling for the minimisation factors with age, sex and onset of pain duration as fixed effects, each with two levels, and study site (10 or more levels) as a random effect. It is possible that controlling for study site will not be possible due to stability of the statistical model and this will be explored. Analysis will produce the absolute risk difference between the two treatment arms with a one-sided 95% confidence interval applying bootstrapping, which can then be assessed against the pre-specified non-inferiority margin of 20%. The number and percentage of children meeting the definition of treatment success at 1 year following randomisation will also be presented.

Individual outcomes that contribute to the composite primary outcome will be presented solely as descriptive statistics within the treatment pathway to which they apply (e.g. recurrent appendicitis is not relevant to the appendicectomy treatment arm). Secondary outcomes that apply to both treatment pathways will be analysed in superiority comparisons between the treatment pathways in ITT analyses, with the exception of adverse events (AEs) for which only descriptive statistics will be provided.

Further details of this, and methods for analysis of secondary outcomes, will be documented in a Statistical Analysis Plan. All analyses will be performed using STATA 19 [33].

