### Trial design {8}

A multi-centre, open-label, parallel-group, non-inferiority randomised controlled trial comparing a non-operative treatment pathway with appendicectomy with internal pilot, health economic evaluation and qualitative sub-study. Both groups of children will receive broad spectrum antibiotics from the point of diagnosis; one group of children will undergo urgent appendicectomy, the other will be treated non-operatively with continuation of broad spectrum intravenous antibiotics. Patients enrolled in the study will be randomised at a ratio of 1:1. See Fig. 1 for a Trial schema overview.

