### Methods in analysis to handle protocol non-adherence and any statistical methods to handle missing data {20c}

The primary analysis will compare the overall ‘non-operative treatment pathway’ versus ‘appendicectomy’ and will take into account whether the initial non-operative approach was successful or not by designating per-protocol treatment switches to appendicectomy as treatment failure. This analysis, based on a comparison of two treatment pathways rather than non-operative treatment versus appendicectomy, reflects the proposed clinical pathway under investigation. It also accounts for treatment switches due to non-operative treatment failure by designating these as a treatment failure at 1 year (the primary outcome). If the non-operative treatment pathway is inferior to appendicectomy, this will be reflected in the numbers of patients who switch to appendicectomy and this will be reflected in the analysis proposed.

The per-protocol analysis will be a secondary analysis to explore the effect of non-adherence to allocated treatment (which are most likely to be due to parents’, children’s or clinicians’ desire to revert to either appendicectomy or non-operative treatment ahead of the trial schedule).

Missing data patterns will be explored to investigate mechanisms of missingness. We will consider the impact of any missing data on the primary outcome, such as sensitivity analyses.

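### The primary analysis set is called ITT but is limited to children with completed data, and it is not stated whether a documented failure counts as completed; either reading can bias the risk difference

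*Protocol article*

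**What the plan says.** In the protocol article, Statistical methods {20a} defines the primary population as all randomised children, whatever treatment they received, who also "have completed data for the outcome and timepoint being analysed". The adjusted risk difference from that set "can then be assessed against the pre-specified non-inferiority margin of 20" per cent.

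Sample size {14} is built on the same set: "this trial will require a total of 318 cases analysed at 1 year (159 per arm"), and then "Allowing for 15% loss to follow up, the recruitment target will be 376 participants (188 per arm").

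On missing data, section {20c} plans to explore patterns and mechanisms of missingness and adds: "We will consider the impact of any missing data on the primary outcome, such as sensitivity analyses". No method is named for the primary estimate.

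Three other sections bear on who has an outcome:
- Outcomes {12} defines success as recovery with none of four listed events, so any one event settles the outcome as failure.
- Section {20c} scores switches to appendicectomy for failed non-operative treatment as failures at 1 year.
- Provisions for post-trial care {30} records suspected recurrences as failures of the non-operative pathway, and has a nurse search hospital records when a visit is missed.

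The note to Table 4 and section {18b} continue data collection after withdrawal unless the family refuses it.

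**The concern.** A set restricted to completed data is a complete-case set, whatever its label. The composite cannot be undone once an event has occurred, and two components are usually known early: index histology, and appendicectomy during the first admission. A child can therefore be a known failure and still lack 1-year follow-up. The words on outcome and timepoint do not say whether such a child is in or out. Sections {20c} and {30} say how an event is scored; {20a} says who enters the analysis.

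The choice matters because the trial turns on one confidence bound against a 20-point margin. Leaving known failures out makes the result depend on whether failing families are harder to follow. Keeping them in, while dropping children who were event-free when lost, over-represents failures even if loss has nothing to do with outcome.

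**Working it through.** **Inputs from the protocol.** Planning rates: "assuming 88% treatment success in the appendicectomy group and 80% in the non-operative group". Margin 20 points; design "with a one-sided 5% significance level and 90% power"; 159 analysed and 188 recruited per arm; allocation 1:1 ("Patients enrolled in the study will be randomised at a ratio of 1:1").

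**Inputs assumed.** The protocol gives neither loss rates by outcome nor the share of lost children whose failure is already documented. Both are varied below. Loss is 15% except where stated.

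**The plan's own figures.** n per arm = [0.88×0.12 + 0.80×0.20] × (1.645 + 1.282)² / (0.20 − 0.08)² = 0.2656 × 8.564 / 0.0144 = 157.96, so 158 against the stated 159. Inflation: 159/0.85 = 187.1, rounded up to 188 per arm, or 376. Both are reproduced.

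**Method.** For true success p, loss L_s among successes, loss L_f among failures and share d of lost failures that are documented and retained:
- retained successes s = p(1 − L_s)
- retained failures f = (1 − p)(1 − L_f + d·L_f)
- analysed success = s/(s + f), on n = 188(s + f)
- P(declare non-inferiority) = Φ[(0.20 − difference)/SE − 1.645], where difference is appendicectomy minus non-operative and SE is unpooled, without covariates.

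False non-inferiority is this probability at a true 88% v 68%.

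**Reading A: known failures without 1-year data are excluded (d = 0).** Loss is 15% in every group except non-operative failures.

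| Loss among non-operative failures | Difference (non-operative minus appendicectomy) at 88% v 80% | P(non-inferiority) at 88% v 80% | False non-inferiority at 88% v 68% |
|---|---|---|---|
| 5% | −9.8 | 79.3% | 1.4% |
| 10% | −8.9 | 85.4% | 2.7% |
| 15% | −8.0 | 90.3% | 5.0% |
| 20% | −7.0 | 94.0% | 8.8% |
| 25% | −6.1 | 96.6% | 14.7% |
| 30% | −5.1 | 98.3% | 23.2% |

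Worked case, last row at the margin: s = 0.68×0.85 = 0.578; f = 0.32×0.70 = 0.224; success = 0.578/0.802 = 72.1% on 150.8 children; SE = 0.0447; Φ[(0.20 − 0.159)/0.0447 − 1.645] = 23.2%.

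Overall loss need not look unusual. Suppose half of non-operative failures are early (assumed). If these are lost at 25% and all other non-operative children at 13%, total non-operative loss is 14.9%, analysed success is 69.5% and false non-inferiority is 9.7%. At 40% and 11%, the figures are 15.6%, 71.7% and 21.3%.

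**Reading B: known failures are kept and event-free losses dropped.** Loss is 15% and unrelated to outcome.
- *Limiting case, all lost children's failures documented (d = 1).* Appendicectomy 0.748/(0.748 + 0.12) = 86.2%; non-operative 0.68/(0.68 + 0.20) = 77.3%. The difference is −8.9 points and power 83.6%. At the margin, 0.578/(0.578 + 0.32) = 64.4%, the difference is −21.8 points and type I error 2.1%.
- *Half documented in both arms.* Difference −8.5 points, power 87.0%, type I error 3.2%.
- *All documented after appendicectomy, half in the non-operative arm.* Difference −7.6 points, power 90.6%, type I error 4.9%. The biases largely cancel.

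**Children involved.** At 15% unrelated loss, 188×0.15 = 28.2 per arm are lost. Of these, 28.2×0.20 = 5.6 non-operative and 28.2×0.12 = 3.4 appendicectomy children would be failures.

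**The case against.** A reader might infer from {20a} that children with a documented failure are deleted, and that the trial is therefore tilted towards non-inferiority. The protocol does not support that. No section says such children are dropped. A child operated on during the first admission and later lost is the case that {20c} scores as a failure at 1 year; {30} does the same for suspected recurrence, and under {12} one event settles the composite. Nor is the direction fixed: under Reading A the bias vanishes if loss is unrelated to outcome, and reverses if failures are easier to trace.

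The scale can also be overstated. Hospital-record searches and continued data collection after withdrawal should recover many outcomes. The complete-case restriction does not leave the trial short of its target either: it was sized for 318 analysed and reaches 90.3% power at 15% unrelated loss.

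Finally, the choice of imputation or tipping-point method normally belongs in the statistical analysis plan, which is not shown. That stands as to detail. It does not cover the analysis set, which the article states under an ITT label and without the rule for documented failures. Sensitivity analyses do not repair a primary estimate, and the kinder reading has its own bias.

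**Conclusion.** The point holds as an ambiguity with consequences on both sides. The primary set is complete-case, and its definition does not say whether a documented event completes the outcome; the rest of the protocol suggests that it does.

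On that likelier reading, the error tends to run against the non-operative arm: up to 0.9 points, about 6 points of power below the stated 90%, and type I error near 2%. It shrinks as fewer lost children's failures are documented, and largely cancels if documentation is poorer in the non-operative arm. On the other reading, type I error at the margin could lie anywhere from about 1.4% to 23% over the assumed loss rates, with 5% if loss is unrelated to outcome.

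These figures rest on a normal approximation without covariates and on assumed loss patterns. They show sensitivity and do not forecast what will happen. With about nine failures expected among lost children (5.6 + 3.4), this should be corrected before outcomes are analysed, but it does not undermine the design.

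**What to change.** In {20a} and the statistical analysis plan:
1. Define the primary set as all randomised children, analysed as allocated.
2. State that a documented component event at any time up to 12 months is a failure, whatever the later follow-up.
3. For children event-free at last contact, use multiple imputation by arm given the time already event-free, which keeps the planned logistic model and bootstrap bound. The alternative is a 12-month risk difference from a time-to-first-failure analysis, with these children censored.
4. Pre-specify a tipping-point sensitivity analysis that makes the imputed outcomes in the non-operative arm progressively worse.
5. Keep the present set as a sensitivity analysis, labelled complete-case.

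Steps 2 and 3 belong together: step 2 alone produces the Reading B bias.

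The cost is wording and modest programming, with no new data. The added assumption is that outcomes are missing at random given arm and time event-free, and the tipping-point analysis tests it.
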